### 2.2 Secondary

1. Peripheral maternal parasitaemia at delivery (microscopic and submicroscopic)
2. Prevalence of *P. falciparum* parasitaemia in cord blood (microscopic and submicroscopic)
3. Prevalence of placental *P. falciparum* infection (histology or blood smear, microscopy and submicroscopic)
4. Mean maternal haemoglobin (g/dL) at delivery
5. Prevalence of maternal anaemia at delivery (< 11g Hb/dL)
6. Prevalence of severe maternal anaemia at delivery (< 7g Hb/dL)
7. Prevalence of neonatal anemia (Hb<12.5 g/dL in case of cord blood, or Hb <13 g/dL in case of peripheral blood )
8. Mean birth weight (in grams)
9. Prevalence of prematurity
10. Number of stillbirths
11. Number of miscarriages
12. Frequency of congenital malformations.
13. Mean gestational age at birth (assessed by Ballard score in the newborn)
14. Incidence of vomiting
15. Incidence of dizziness
16. Frequency of drug adverse reactions
17. Incidence of clinical malaria during pregnancy
18. Incidence of overall maternal admissions/outpatient attendances
19. Neonatal and infant mortality rate

---

Only in a subsample of participants

20. Incidence of clinical malaria in the first year of life
21. Peripheral maternal parasitaemia 1 month after end of pregnancy (microscopic and submicroscopic)

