## 3 Study design overview

This is a randomized open-label superiority 3 arms trial to compare 2-dose MQ with two dose of SP as IPTp in the prevention of the adverse effects of malaria during pregnancy and to compare MQ tolerability of 2 different MQ administration regimens. The three arms of the study are:

1. IPTp with SP (SP)
2. IPTp with MQ given as full dose (MQf)
3. IPTp with MQ given as an split dose (MQs)

The table 1 shows the visits and procedures schedules to the mother and the table 2 shows the visits and procedures schedule to the child.

---

At visit 4, approximately one month after end of pregnancy

Table 1: Maternal visits and procedures schedule

| Study Procedures                                    | Visit 1
Enrollment | Visit 2 | Visit 3
Delivery | Visit 4
1 Month | Unscheduled
visits | Household
visits |
|-----------------------------------------------------|-----------------------|---------|---------------------|--------------------|-----------------------|---------------------|
| Inclusion/Exclusion criteria                        | X                     |         |                     |                    |                       |                     |
| Written informed consent                            | X                     |         |                     |                    |                       |                     |
| Demographics/Medical history                        | X                     |         |                     |                    |                       |                     |
| Record of concomitant medication/
Adverse events | X                     | X       | X                   | X                  | X                     |                     |
| Physical examination / Clinical                     | X                     |         |                     |                    | X                     |                     |
| Gestational Age                                     | X                     | X       | X                   |                    | X                     |                     |
| Temperature                                         |                       |         |                     | X                  | X                     |                     |
| Blood Pressure                                      |                       |         | X                   |                    | X                     |                     |

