Continuous variables will be compared between groups and adjusted for covariates and possible confounders using ordinary least square regression. Variables will be transformed to the logarithm scale if normality is improved and result presented as Proportional Difference.

Incidence of clinical malaria, overall admissions and outpatient attendances will be estimated as the number of episodes over the time at risk. Time at risk is estimated as the time from the start of follow up (recruitment in mothers, day of birth in infants) until the end of follow-up (visit one month after

[figure not shown]

Figure 2: Rules for Superiority

delivery for mothers and visit after 12 months of age in infants) or withdrawal due to censoring or death, whatever occurs first. In order to avoid to count twice the same episode of clinical malaria, subjects will not contribute to the denominator nor the numerator during an arbitrary period of 28 days after an event of clinical malaria is defined. For admissions and outpatient attendances a maximum of one episode per day will be allowed. The total number of events will be compared between groups using negative binomial regression to take into account a possible extra Poisson variation due to different frailty of the subjects. The comparison will be expressed as Relative Rate (RRate)

For the ATP cohorts, in order to allow for center differences, regression models will include site as covariate as well as season. The definition of season will be independent for each site. Interaction between site and treatment to evaluate homogeneity will be estimated using a combined test for the interaction terms. In addition of the adjusted results, the crude results for ATP cohort will be also presented.

For the efficacy, analysis will be presented for ATP and ITT populations. The analysis of ITT population are not adjusted for possible confounders. For Safety and Tolerability, analysis will be presented for Safety and ITT populations, all of them unadjusted. See section 6 for the classification of endpoints efficacy, safety or tolerability.

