†Submicroscopic infection determined only in a subsample.

Table 13: Secondary endpoints (continous variables)

| Variable                                 | Group    | N            | mean           | sd                          | Diff (95% CI)     | p-value |
|------------------------------------------|----------|--------------|----------------|-----------------------------|-------------------|---------|
| Maternal Hemoglobin (g/dL) when.. | MQ
SP | ####
#### | ##.##
##.## | ##.##
##.##              | #.## (#.##; #.##) | #####   |
| Variable                                 | Group    | N            | Geometric mean | IQR                         | PDiff (95% CI)    | p-value |
| Gestational age (weeks) when..    | MQ
SP | ####
#### | ##.##
##.## | ##.##:##.##
##.##: ##.## | #.## (#.##; #.##) | #####   |

Diff = difference between groups. PDiff= Proportional difference between group. IRQ: Interquartilic range

Table 14: Secondary endpoints (incidence)

| Variable                                       | Group | N    | Events | PYAR | Incidence | RRate (95% CI)    | p-value |
|------------------------------------------------|-------|------|--------|------|-----------|-------------------|---------|
| Clinical malaria during pregnancy              | MQ    | #### | ##     | #### | #.####    | #.## (#.##; #.##) | #.####  |
|                                                | SP    | #### | ##     | #### | #.####    |                   |         |
| Overall number of maternal hospital admissions | MQ    | #### | ##     | #### | #.####    | #.## (#.##; #.##) | #.####  |
|                                                | SP    | #### | ##     | #### | #.####    |                   |         |
| Outpatient number of maternal visits           | MQ    | #### | ##     | #### | #.####    | #.## (#.##; #.##) | #.####  |
|                                                | SP    | #### | ##     | #### | #.####    |                   |         |

RRatio: Relative Ratio, N: Number of subject per group, PYAR: Person years at risk.

Table 15: Secondary endpoints (endpoints for neonatal mortality)

| Variable                 | Group | N    | n(%)      | RR (95% CI)       | p-value |
|--------------------------|-------|------|-----------|-------------------|---------|
| Perinatal mortality      | MQ    | #### | ## (##.%) | #.## (#.##; #.##) | #.####  |
|                          | SP    | #### | ## (##.%) |                   |         |

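### The incidence of clinical malaria during pregnancy is planned over a window that runs to one month after delivery, a longer period than the endpoint names

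*SAP*

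**What the plan says.** SAP Section 2.2 lists secondary endpoint 17 as "Incidence of clinical malaria during pregnancy". In Section 6.3.2, Table 14 reports it in a row labelled "Clinical malaria during pregnancy", with events, person-years at risk, incidence and relative rate.

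Section 5 defines the calculation once for three outcomes: "Incidence of clinical malaria, overall admissions and outpatient attendances will be estimated as the number of episodes over the time at risk". Time at risk begins at "the start of follow up (recruitment in mothers, day of birth in infants") and runs "until the end of follow-up (visit one month after". Figure 2 interrupts the sentence there, and it continues "delivery for mothers and visit after 12 months of age in infants) or withdrawal due to censoring or death, whatever occurs first". For mothers, then, the window closes at the postpartum visit, which a footnote in Section 3 places "At visit 4, approximately one month after end of pregnancy".

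The only exclusion specific to malaria follows an episode: "subjects will not contribute to the denominator nor the numerator during an arbitrary period of 28 days after an event of clinical malaria is defined". No rule refers to the end of pregnancy.

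**The concern.** The endpoint's name and its risk window describe different periods. The name does not look like loose wording. Endpoint 21 in the same list is explicitly a post-pregnancy measure, and endpoint 18 (maternal admissions and outpatient attendances) carries no pregnancy limit, so the SAP does separate the two periods elsewhere. For endpoint 18 the longer window is consistent with the name; for endpoint 17 it is not.

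A programmer who follows Section 5 would report postpartum malaria in a row labelled as malaria in pregnancy. One who applies the label to the episodes but Section 5 to the person-time would divide pregnancy episodes by time in which none can occur. Neither gives the named quantity. Section 6.3 classes malaria disease among the efficacy endpoints and the trial is open-label, so the choice should be fixed before the data are analysed.

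**Working it through.** The SAP states no malaria rate, event count or power for this endpoint, so there is no planned figure to reproduce. The mismatch follows from the text alone. Its possible size needs assumptions.

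**Assumptions (not in the SAP).** Delivery at 39 weeks; postpartum follow-up of 4.3 weeks; recruitment at 13, 22 or 28 weeks; a true pregnancy rate ratio (MQ/SP) of 0.70; the same follow-up in both arms; the 28-day gaps after episodes ignored. Let T = 39 − gestational age at recruitment, k = the SP postpartum rate divided by the SP pregnancy rate, and ρ = the MQ/SP ratio after delivery.

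**Share of person-time after delivery** = 4.3/(T + 4.3).

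**Both periods counted, as the text reads.**
- SP rate relative to its pregnancy rate = (T + 4.3k)/(T + 4.3)
- Rate ratio = (0.70T + 4.3kρ)/(T + 4.3k)

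With k = 1:

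| Recruited at | T (weeks) | Postpartum share | Ratio, ρ = 0.70 | Ratio, ρ = 0.85 | Ratio, ρ = 1.00 |
|---|---|---|---|---|---|
| 13 weeks | 26 | 4.3/30.3 = 14.2% | 0.700 | 21.855/30.3 = 0.721 | 22.5/30.3 = 0.743 |
| 22 weeks | 17 | 4.3/21.3 = 20.2% | 0.700 | 15.555/21.3 = 0.730 | 16.2/21.3 = 0.761 |
| 28 weeks | 11 | 4.3/15.3 = 28.1% | 0.700 | 11.355/15.3 = 0.742 | 12.0/15.3 = 0.784 |

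Varying the postpartum base rate:
- k = 0.5: the SP rate becomes 28.15/30.3 = 0.929 (13 weeks) to 13.15/15.3 = 0.859 (28 weeks) of the pregnancy rate. With ρ = 1 the ratio is 20.35/28.15 = 0.723 to 9.85/13.15 = 0.749.
- k = 1: the SP rate is unchanged. With ρ = 1 the MQ rate rises by 0.743/0.70 = 1.06 to 0.784/0.70 = 1.12.
- k = 1.5: the SP rate becomes 32.45/30.3 = 1.071 to 17.45/15.3 = 1.141. With ρ = 1 the ratio is 24.65/32.45 = 0.760 to 14.15/17.45 = 0.811.
- Any k with ρ = 0.70: the ratio stays 0.70.

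**Only pregnancy episodes counted, over the longer window.** Each arm's rate is multiplied by T/(T + 4.3): 26/30.3 = 0.858, 17/21.3 = 0.798 and 11/15.3 = 0.719. The rate is understated by 14%, 20% and 28%. The factor cancels in the ratio if the arms have the same share of postpartum time.

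**The case against.** The strongest reply is that Section 5 is internally coherent. It divides episodes by time at risk, and its 28-day exclusion removes numerator and denominator together, so both share one window. That window is the full maternal follow-up and matches the other two rows of Table 14. On this view only the label is wrong. This stands in part: counting pregnancy episodes alone over the longer time is the less natural reading, and the SAP does not show whether the label or the window was intended. It does not remove the mismatch, because a coherent rate over the longer window is still not the named endpoint.

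Three stronger readings are tempting, and the SAP supports none of them.

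- **That incidence is understated in every arm.** This holds only under the less natural reading. With postpartum episodes counted, the rate can rise, fall or stay the same.
- **That the rate ratio is diluted.** This needs the MQ/SP ratio to move toward 1 after delivery. Section 5 itself refers to the long half-life of mefloquine, so a complete loss of effect at delivery is not an obvious default. The SAP gives no data on the point.
- **That a leading secondary endpoint is compromised.** The list in Section 2.2 is unranked and no decision rule depends on endpoint 17.

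A reader may also note from Table 1 that the postpartum visit has a scheduled blood smear, whereas smears at the first two visits are only for women reporting sick. The SAP does not say whether a finding at the postpartum visit could count as clinical malaria, so unequal ascertainment cannot be asserted.

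**Conclusion.** The inconsistency is certain and rests on no assumption: the planned incidence is for pregnancy plus about a month, while the endpoint and table row say pregnancy. Its numerical effect cannot be known from the SAP. Under the assumptions above, 14% to 28% of maternal person-time falls outside the named period. With postpartum episodes counted and equal base rates, a pregnancy ratio of 0.70 is reported as anything from 0.70 (effect fully persists) to 0.74–0.78 (no postpartum effect, by time of recruitment). If only pregnancy episodes were counted, incidence would be 14% to 28% too low with the ratio about unchanged. This is a limited but real fault in one secondary efficacy endpoint. The admissions and outpatient analyses are not touched by it.

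**What to change.** Add one sentence to Section 5: for endpoint 17, both the episode count and the time at risk end at the end of pregnancy (delivery or miscarriage), withdrawal or death, whichever is first. Keep the window to the postpartum visit for admissions and outpatient attendances. Postpartum clinical malaria can be reported as a separate line if wanted.

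If the longer window is what was intended, leave Section 5 as it is and rename endpoint 17 and the Table 14 row so that they state recruitment to one month after the end of pregnancy. Either route cures the contradiction, but one must be chosen.

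The first option costs a change of censoring date and somewhat fewer episodes and person-years, hence a slightly less precise relative rate. Delivery dates are already among the Section 7 listings; the date of a miscarriage is not named there and would have to come from the outcome or withdrawal record. The second option costs only wording, but gives up a pregnancy-specific rate.

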### 4.2 Intention to Treat (ITT)

This population includes all randomized women. Following the intention-to-treat principle, patients will be analyzed according to the preventive treatment they were assigned to at randomization. This population is the target for the analysis of efficacy.

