## 5 Statistical methods

For the primary analysis of efficacy, the statistical analysis will follow a sequential approach. First, hypotheses of non-inferiority between the proportion of LBW in the MQ groups and the SP group will be tested assuming as equivalence a 25% reduction or greater in LBW prevalence in the MQ groups. If non-inferiority between MQ and SP is achieved, then an analysis for superiority will be conducted comparing the MQ and SP groups using a two-sided test. Given the long half life of MQ, it has been assumed that MQ efficacy to prevent LBW will be equal in the full dose and split dose groups.

Interpretation of non-inferiority is based on the confidence intervals (CI). If the upper limit of the confidence interval (CI) of the Relative Risk (RR) MQ/SP is below 1.25, (25% of the RR) the MQ arms will be considered as non-inferior compared with SP (See figure 1). In case the upper limit of the CI is above 1.25, the trial is inconclusive as the non-inferiority hypothesis can't be rejected. If both the lower limit of the CI is below 1, the MQ treatment is considered superior to SP (See figure 2).

[figure not shown]

Figure 1: Rules for Non-inferiority

No adjustment of p-values are necessary to this switch as the “delta“ has been pre-specified, and then the interpretation based on confidence intervals can support the interpretation of non-inferiority. It is acceptable to calculate the p-value associated with a superiority test and to evaluate whether this is sufficiently small to reject convincingly the hypothesis of no difference. There is no multiplicity that affect this interpretation because in statistical terms it corresponds to a simple closed test procedure (Committee for Proprietary Medicinal Products CPMP, Points to consider on switching between superiority and non-inferiority, CMP/EWP/482/99, July 2000).

Proportions will be compared between groups using fisher exact test and presented as Risk ratio (RR) or reduction of the RR ( $1 - RR * 100\%$ ) if RR lower than 1. Adjustment for covariates and possible confounder are done using binomial regression with log link, and using robust estimates of the covariance (huber method) using the method proposed by Zou (Zou G., A modified poisson regression approach to prospective studies with binary data. American Journal of Epidemiology. 2004;159(7):702-706).

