For the ITT analysis of primary endpoint, which includes all women recruited in the study, missing values for low birth weight will be imputed as follow: For those women with miscarriage, the event will be considered as failure and they will be assigned as having LBW. For those lost to follow-up or withdraw before delivery a sensitivity analysis of worse case scenario assuming all lost of follow-up and withdrawn women having a LBW, best case scenario assuming that none have LBW and worst case scenario assuming as LBW all missing values, will be presented. In case there were countries without malaria events, a sensitivity analysis not including those countries will be also presented.

The assumption that  $MQ_s$  and  $MQ_f$  have a similar effect on the LBW will be explored by inspection of the 90% confidence intervals of the comparison between  $MQ_s$  vs  $MQ_f$  in the ATP population. If the assumption of both MQ groups are similar is rejected, then comparison between  $MQ_s$  vs SP and  $MQ_f$  vs SP will be presented instead.

For the primary outcome, the weight of children born taken after delivery but before the seven days of life are transformed according to the method proposed by ... *Greenwod* (*to be completed*) to include in

A regression analysis of the weight and day after delivery

the analysis as if they were taken at birth. Maternal and new born haemoglobines from visit 3(Delivery) not taken in the date of the delivery will not be included in the analysis of these outcomes.

The gestational age will be based on the Ballard score, but in case of missing, it will be based on the gestational age calculated with the fundal height at recruitment.

For the frequency of vomiting, dizziness, prematurity, the proportion of women with those outcomes will be compared using the methods described for proportions before.

For the tolerability, only those vomiting and dizziness judged by the investigators to be related to the medication will be included in the analysis except vomiting during the first 60 minutes after a dose of IPTp that will always be considered related to medication.

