## 6.3 Efficacy (ATP Adjusted, ATP crude, ITT)

Efficacy endpoints refers to the effect of MQ on the low birth weight, different forms of malaria infection, malaria disease and anaemia. Analysis are presented adjusted for ATP and also crude for ATP and ITT populations. For the primary endpoint, the sensitivity analysis using best, worst and maximum bias scenarios will be presented. Secondary endpoints will be presented crude for ITT population, and adjusted for country in ATP population. If interaction between country and treatment is significant, secondary endpoints will be also presented by country.

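### No missing-outcome scenario for the primary endpoint is adverse to MQ alone; with similar loss by arm the worst case can favour non-inferiority, and the announced maximum-bias scenario is not defined

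*SAP*

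**What the plan says.** Section 4.2 of the SAP defines ITT as all randomized women and adds: "This population is the target for the analysis of efficacy". Section 5 gives the decision rule. "If the upper limit of the confidence interval (CI) of the Relative Risk (RR) MQ/SP is below 1.25", MQ is non-inferior; otherwise the trial is inconclusive.

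For the ITT analysis of LBW, Section 5 then deals with missing outcomes:

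- Miscarriage: "the event will be considered as failure and they will be assigned as having LBW".
- Lost or withdrawn before delivery, first scenario: "worse case scenario assuming all lost of follow-up and withdrawn women having a LBW".
- Second and third scenarios: "best case scenario assuming that none have LBW and worst case scenario assuming as LBW all missing values, will be presented".

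No scenario mentions treatment arm. Section 6.3 describes the same set with other names: "the sensitivity analysis using best, worst and maximum bias scenarios will be presented". The term maximum bias appears nowhere else in the SAP.

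**The concern.** The primary claim runs in one direction: MQ must not be more than 25% worse than SP on the RR scale. Missing data threaten it if the MQ women without a birth weight fared worse than the SP women without one. A scenario that gives both arms the same outcome cannot represent that.

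There is also a scale effect. Counting every missing woman as LBW adds a similar absolute risk to both arms when loss is similar. If the observed RR is above 1, the ratio then moves towards 1. The added events also shrink the standard error of the log RR. The analysis labelled worst case can then be the easiest to pass, and a reader of the report could take it as strong support for non-inferiority.

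Finally, an analysis announced in Section 6.3 but not defined under that name in Section 5 can be filled in more than one way after the data are seen.

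**Working it through.** **Inputs from the SAP.** Limit 1.25 on the upper confidence limit of RR MQ/SP (Section 5); 95% interval (Table 9; Table 11 heads its MQ vs SP column with 90%); pooled MQ against SP; the three scenarios above.

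**Assumed inputs.** The SAP gives no sample size, allocation ratio, LBW rate or expected loss, so it has no figure to reproduce. I take SP n = 1500, pooled MQ n = 3000, SP LBW proportion p0 = 0.12, and missing fractions m1 (MQ) and m0 (SP) of 5% to 15%. Miscarriages are left out for simplicity.

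**Formulas.** With observed RR equal to R:

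- Complete case: RR = R.
- None LBW: RR = R(1−m1)/(1−m0), which stays at R when m1 = m0.
- All missing LBW: RR = [p0·R(1−m1) + m1] / [p0(1−m0) + m0].
- By arm, adverse to MQ: missing MQ = LBW, missing SP = not LBW.
- With a of n1 MQ women and b of n0 SP women having LBW, SE(log RR) = √(1/a − 1/n1 + 1/b − 1/n0), and the interval is RR·exp(±1.96·SE).

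If nobody is missing apart from loss and withdrawal, the first and third SAP scenarios coincide, as they do here.

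**Main case: R = 1.20, 10% missing in each arm.** Observed: SP 0.12 × 1350 = 162 LBW; MQ 0.144 × 2700 = 388.8 LBW. Missing: SP 150, MQ 300.

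| Scenario | MQ | SP | SE | RR (95% CI) | Upper limit < 1.25? |
|---|---|---|---|---|---|
| Complete case | 388.8/2700 | 162/1350 | 0.0874 | 1.20 (1.01-1.42) | no |
| None LBW | 388.8/3000 | 162/1500 | 0.0880 | 1.20 (1.01-1.43) | no |
| All missing LBW | 688.8/3000 | 312/1500 | 0.0605 | 1.10 (0.98-1.24) | **yes** |
| By arm, adverse to MQ | 688.8/3000 | 162/1500 | 0.0814 | 2.13 (1.81-2.49) | no |

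The reversal does not depend on p0 = 0.12. At p0 = 0.10 the complete-case 1.200 (0.992-1.451) becomes 1.095 (0.965-1.241). At p0 = 0.15, 1.200 (1.032-1.395) becomes 1.115 (0.999-1.244).

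**Where the effect goes the other way (p0 = 0.12).**

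- More loss on MQ (15% against 10%), R = 1.0. All missing LBW gives 756/3000 against 312/1500, which is 1.21 (1.08-1.36) and fails. Complete cases give 1.00 (0.84-1.20) and pass.
- R = 0.8, 10% missing in each arm. All missing LBW raises the upper limit from 0.96 to 1.01.

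**Is the arm-specific extreme useful alone?** Take R = 1.0 and 5% missing in each arm. Observed LBW: MQ 342 of 2850, SP 171 of 1425. The scenario adverse to MQ gives (342 + 150)/3000 against 171/1500, which is 1.44 (1.22-1.69). It fails at equality with little loss, so it is an outer bound and not a discriminating test.

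**What a tipping-point table adds.** Take R = 1.0 and 10% missing in each arm, and let 12% of missing SP women have LBW (180/1500 in total). If 18% of missing MQ women have LBW (378/3000), the RR is 1.05 (0.89-1.24) and passes. At 20% (384/3000) it is 1.07 (0.90-1.26) and fails. The reader sees how large a difference among the missing would overturn the claim. These intervals treat imputed outcomes as observed.

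**The case against.** A reader might go further than the SAP supports in four ways.

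- **That every scenario pulls the RR towards 1.** This is not so. Counting none as LBW leaves the RR unchanged under equal missingness, and under unequal missingness same-value imputation can move it away from 1 in either direction.
- **That heavier loss on MQ, for example through intolerance, would go unnoticed.** It would not. In that setting all-LBW is the hardest of the SAP's scenarios, and Tables 3 to 7 show withdrawals by arm, with reasons. The untested case is similar loss with different outcomes among the lost.
- **That the trial's false-positive rate is inflated.** Section 5 says that the scenarios will be presented as a sensitivity analysis and attaches no decision to them. The harm is misleading reassurance, and any error rate would rest on assumed inputs.
- **That Section 5 defines one scenario twice and omits another.** The worse case covers lost and withdrawn women, and the worst case covers all missing values, so the sets can differ. Section 5 has three scenarios and Section 6.3 three names, so the third may be the one meant by maximum bias. What is established is a mismatch of labels.

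It is also fair to say that an arm-specific extreme fails almost whatever the data show. That stands, and it is why the tipping-point table should be the main check.

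**Conclusion.** The point holds in a limited form. From the text alone, no stated scenario distinguishes the arms, and maximum bias has no definition under that name. By arithmetic, with similar loss and an observed RR above 1, the analysis labelled worst case can pass 1.25 where complete cases fail. The size, an upper limit moving from 1.42 to 1.24, rests on the assumed sample size, 2:1 allocation, LBW rate and 10% loss. The direction follows from the formula. It does not hold with appreciably more loss on MQ or with an observed RR well below 1. The primary test itself is not shown to be wrong. This should be corrected because the plan, followed as written, can report a lenient check under the name worst case.

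**What to change.** In SAP Section 5:

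1. Define maximum bias by arm, in both directions: missing MQ = LBW with missing SP = not LBW, and the reverse. Describe these as outer bounds.
2. Add, as the main robustness check, a tipping-point table over the LBW proportion among missing women in each arm separately, marking where the upper limit of the RR crosses 1.25.
3. State that the scenarios counting missing women in both arms as LBW do not by themselves support non-inferiority.
4. Use one set of scenario names in Sections 5 and 6.3, and say which women each covers.

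The cost is some wording and one extra table, with no new data. The downside is that robustness to missing outcomes may look less favourable.

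### The pooled MQ vs SP primary comparison can be replaced by two arm-specific ones after a look at outcome data, with no rejection limits, no success rule after the split and no multiplicity adjustment

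*SAP*

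**What the plan says.** Section 5 of the SAP starts from the premise that "it has been assumed that MQ efficacy to prevent LBW will be equal in the full dose and split dose groups", so the default primary comparison is pooled MQ against SP. Non-inferiority is met if "the upper limit of the confidence interval (CI) of the Relative Risk (RR) MQ/SP is below 1.25", and superiority is then tested two-sided. Section 5 gives no confidence level for either step.

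Later in section 5 the premise is put to a check. It "will be explored by inspection of the 90% confidence intervals of the comparison between" the split-dose arm (MQs) and the full-dose arm (MQf), "in the ATP population". The consequence follows: "If the assumption of both MQ groups are similar is rejected, then comparison between" MQs and SP, and between MQf and SP, "will be presented instead".

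Three other places bear on this:

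- Section 4.2 says of ITT: "This population is the target for the analysis of efficacy".
- In section 6.3.1, Table 9 (pooled MQ vs SP) carries a 95% CI. Table 11 (by arm) heads both its MQ vs SP column and its MQs vs MQf column with a 90% CI.
- The only multiplicity text, in section 5, says that no adjustment is needed when moving from non-inferiority to superiority, because that sequence is a closed test.

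**The concern.** The comparison that answers the primary question is chosen after the outcome has been seen, and the rule for choosing it is incomplete. The contrast, the CI level and the population of the check are fixed. The limits that would count as rejection are not. Two analysts could follow the text faithfully and report different primary comparisons from the same data.

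After a split there are two chances to succeed against SP. The plan does not say whether one success is enough, and it makes no adjustment. The closed-test argument is sound for one MQ vs SP comparison taken from non-inferiority to superiority. It does not reach a pair of arms, or the choice between pooled and separate analyses.

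The check is made in a population other than the efficacy target. ATP is defined by events after randomisation, and two of its exclusions (only a half dose of MQs, and more than 48 hours to the second half) can apply only to the split-dose arm, which is one of the two arms being compared. At stake is the false-claim rate for LBW, and whether the reported primary result was fixed in advance.

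**Working it through.** **No plan figure to reproduce.** The SAP states no sample size, LBW rate, allocation ratio or numerical alpha.

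**Inputs from the SAP:** margin RR 1.25; 90% CI for MQs vs MQf; 95% CI in Table 9, which implies one-sided 0.025; 90% CI for MQ vs SP in Table 11, which would imply one-sided 0.05.

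**Assumptions:** equal arms; MQs and MQf truly identical and on the null boundary (RR = 1 for superiority, 1.25 for non-inferiority); LBW between 8% and 18%; 1000 to 1500 women per arm; one population for check and test. Superiority is taken to mean that the whole CI lies below 1.

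**Step 1: two unadjusted comparisons sharing the SP arm (correlation 0.5).** The probability of at least one false success is 0.0454 with 95% CIs and 0.0878 with 90% CIs. Under independence it would be 1 − 0.975² = 0.0494 and 1 − 0.95² = 0.0975.

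**Step 2: the whole procedure, if rejection means that the 90% CI excludes 1.** Let S, F and C be the log risks in MQs, MQf and SP, each with variance s² = (1 − p)/(pn). The check uses S − F and the pooled test uses (S + F)/2 − C. Their covariance is (s² − s²)/2 = 0, so with identical MQ arms they are independent. The split occurs with probability 0.10. If either arm alone can support a claim:

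P(false claim) = 0.90 × 0.025 + 0.10 × P(at least one arm passes, given a split)

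A simulation of 1,000,000 draws gives 0.147 for the last factor with 95% CIs and 0.244 with 90% CIs. Hence:

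- 95% CIs: 0.0225 + 0.0147 = 0.0372 (simulated directly: 0.0370)
- 90% CIs: 0.0225 + 0.0244 = 0.0469 (simulated directly: 0.0467)

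In this normal approximation neither result depends on p or n. Three-arm trial simulations at 12% LBW and 1500 per arm, RR = 1, give 3.8 to 3.9% and 4.8%, against 2.6% for pooled-only analysis.

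**Step 3: the same rule, but both arms must succeed after a split.** The error is about 2.3%. Almost all of it is the unsplit part, 0.90 × 0.025 = 2.25%.

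**Step 4: an equivalence-type reading.** Suppose the plan splits unless the 90% CI lies within 0.80 to 1.25. The SAP gives no such range for MQs vs MQf. At 10% or 15% LBW and 1000 or 1500 per arm, truly identical arms are split with probability 0.357 to 0.985. With either-arm success and 95% CIs the error is 4.5 to 4.8%. If both arms must succeed it is about 1.2% (12% LBW, 1500 per arm).

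**Step 5: what the CI level does to the margin.** At 10% LBW and 1000 per arm, the SE of a per-arm log RR is √(2 × 0.9/(0.1 × 1000)) = √0.018 = 0.134. The largest estimate that passes RR < 1.25 is 1.25 × exp(−1.645 × 0.134) = 1.00 on a 90% CI and 1.25 × exp(−1.96 × 0.134) = 0.96 on a 95% CI.

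**The case against.** The strongest objection is that inflation is not a necessary result of the text. Section 5 speaks of the MQ arms in the plural, which may mean that both must meet the rule. Step 3 shows that the error then stays below nominal. This stands. A reader might infer that the plan as written raises the false-claim rate, but it does so only if one arm suffices, and the SAP does not say which applies.

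A reader might also infer that the primary comparison is shown with 90% CIs. It is not: Table 9, the default primary display, uses 95%. Table 11 as extracted has a single MQ vs SP cell, which may be pooled or per arm, and a shell heading is weak evidence of a decision level. What stands is that the two tables disagree and section 5 does not settle it.

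The conditional figures (15% and 24% given a split) should not be headlines. They apply to an event that occurs in 10% of trials. They also assume one population: if ATP is taken as 70% of ITT, 15% falls to about 12%, and the overall error with 95% CIs falls from 3.8% to 3.6%. Nor does the check respond only to an arm that looks unusually good. It is symmetric and is triggered equally by an arm that looks unusually bad.

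The split rates in step 4 depend on a borrowed range and on the assumed LBW. At 1500 per arm that reading splits in 23% of trials at 18% LBW and in 88% at 8%. They show only how much the missing limits matter.

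**Conclusion.** The point holds. A data-driven switch of the primary comparison is written into the plan without rejection limits, without a success rule afterwards and without multiplicity control. The check is based on ATP while efficacy targets ITT, and the CI level for MQ vs SP differs between Tables 9 and 11. These defects are in the text and need no simulation.

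The size is moderate and conditional. If the 90% CI excluding 1 triggers the split and either arm suffices, the false-claim probability is about 3.8% against 2.5% nominal with 95% CIs, or about 4.8% if Table 11's 90% CIs were used for decisions. An equivalence-type trigger gives about 4.5 to 4.8% with 95% CIs. If both arms must succeed there is no inflation. All of these rest on the assumptions listed with the calculation. It should be corrected before analysis because it governs the primary endpoint.

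**What to change.** State in section 5 that pooled MQ vs SP in ITT, with a two-sided 95% CI, is the primary analysis whatever the MQs vs MQf comparison shows. Always present MQs vs SP and MQf vs SP as secondary, with 95% CIs, and MQs vs MQf as descriptive, where a 90% CI is acceptable. Change the MQ vs SP column of Table 11 to 95%.

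If the switch is kept, state its numerical rejection limits, base it on the same population as the primary analysis, and say whether one arm or both must succeed after a split. If one arm is enough, use Holm or Bonferroni (Bonferroni: one-sided 0.0125 each, that is 97.5% CIs). Such an adjustment controls the pair as if it had been fixed in advance. It does not undo the selection made by the check, which is why keeping the pooled comparison is cleaner.

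The cost is a few sentences and one column heading, with no change to data collection. The small downside is that, if the two regimens truly differ, the primary estimate is their average. The per-arm results beside it keep the difference visible.
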